### 2.10. Data analysis

Data analysis will be carried out using the Statistical Package for Social Sciences version 26 (SPSS-26, Inc., Chicago, IL, USA). Descriptive statistics for sociodemographic, clinical, and alcohol use characteristics, AUDIT, PACS, HAM-D, and HAM-A scores, and ERP will be computed. For nominal and ordinal data, these will be presented in frequency and percentage. For continuous data, it will be presented as mean and standard deviation if the variable is normally distributed. While for non-normally distributed data, it will be presented as median and interquartile range. The normality of the data will be determined by Shapiro–Wilk test.

As for the assessment of the primary outcome, one-way ANOVA with false discovery rate adjustment is used to compare the mean of the outcomes (PACS, average number of drinks during drinking days, frequency of binge drinking in the previous week, and the number of hazardous drinks per day or per week) between the three groups (VRET, ACT, and control groups) at each specific time point (t_0_, t_1_, t_2_, and t_3_). While for the main analysis, mixed ANOVA is used to evaluate the interaction of intervention and time on the outcomes will be computed (outcomes: PACS, average number of drinks during drinking days, frequency of binge drinking in the previous week, and the number of hazardous drinks per day or per week; interaction: intervention × time; whereby time is the within-subject factor, while intervention is the between-subject factor). The main effect of the interaction will be presented as estimated marginal mean and standard error of mean. The primary outcome assessment will follow the intent-to-treat principle. The data analysis for the secondary outcomes (AUDIT, HAM-D, and HAM-A scores and ERP) will be analyzed in the same way as the primary outcomes. Statistical significance is set at *p* < 0.05 and is two-tailed.

As for the management of missing data, if there is only 5% of missing data or less, it will be ignored and data analysis will proceed. However, if the missing data are from 5 to 40% and are missing randomly, multiple imputations with restricted maximum likelihood estimates will be performed using Stata 15, to estimate the missing values. However, if the missing data are more than 40% or are completely randomly missing or non-randomly missing, data analysis of the remaining data will proceed, and the missing data issue will be reported under the limitation of the study (46).

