### 2.9. Measures

This study follows the Standard Protocol Items: Recommendations for Intervention Trials (SPIRIT) 2013. The checklist for SPIRIT is included in Appendix 3. The schedule for assessments in this study is summarized in Table 1. There will be four timelines of assessment. Baseline assessment (t_0_) commences after the randomization of participants into the three intervention groups (VRET, ACT, and control groups), wherein the sociodemographic, clinical, and alcohol use characteristic questionnaire, Alcohol Use Disorder Identification Test (AUDIT), Penn Alcohol Craving Scale (PACS), Hamilton Anxiety Rating Scale (HAM-A), and Hamilton Depression Rating Scale (HAM-D) are administered, while event-related potential (ERP) detection in electroencephalogram (EEG) is performed in the participants. Then, during follow-up assessment, such as t_1_ = 4 weeks (immediately after completion of intervention), t_2_ = 12 weeks (8 weeks after completion of intervention), and t_3_ = 24 weeks (20 weeks after completion of intervention), the questionnaires are re-administered to the participants which include alcohol use characteristics, AUDIT, PACS, HAM-D, and HAM-A, while ERP detection in EEG is re-assessed. The serial assessments will be carried out by a research assistant who is not involved in the research project and does not know about the objectives of the study. The research assistant will receive some training on the administration of the measures before the data collection begins. To ensure that the participants complete the serial assessments and interventions, an appointment card is given to each participant with the next appointment date written on the card. Emails and messages will be distributed 3 days prior to the appointment to remind the participants regarding the appointment date, and if any participant does not reply, a phone call will be made a day before the appointment date.

**Table 1 T1:** Schedule of assessments of the study outcome measures.

	**Enrollment**	**Allocation**	**Post-allocation**		
**Time**	* **–t** _1_ *	***t**_0_* **(0 week)**	* **t** _1_ * **(4 weeks)**	***t**_2_* **(12 weeks)**	* **t** _3_ * **(24 weeks)**

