**(2) Primary outcomes:**					
(a) Penn Alcohol Craving Scale (PACS)		X	X	X	X

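### The supporting visit-wise ANOVAs test the randomised groups at t0 and leave each patient's t0 score out of the t1 to t3 comparisons: valid, but inefficient

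*Protocol article*

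**What the plan says.** Section 2.10 of the protocol article gives two layers of analysis for PACS and three drinking measures.

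- **Visit-wise layer.** "one-way ANOVA with false discovery rate adjustment is used to compare the mean of the outcomes", the comparison being made "between the three groups (VRET, ACT, and control groups) at each specific time point (t_0_, t_1_, t_2_, and t_3". No covariate is named, and the text does not say which tests form the FDR family.
- **Main layer.** "for the main analysis, mixed ANOVA is used to evaluate the interaction of intervention and time on the outcomes", with time as the within-subject factor and intervention as the between-subject factor.

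AUDIT, HAM-D, HAM-A and ERP "will be analyzed in the same way as the primary outcomes", so both layers carry over to them. On the threshold: "Statistical significance is set at *p* < 0.05 and is two-tailed".

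Table 1 lists "Penn Alcohol Craving Scale (PACS") as the primary outcome and schedules it at t0, t1, t2 and t3, so every assessed patient should have a baseline value. Section 1.6.1 describes t0 as preceding the intervention.

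**The concern.** Two features of the visit-wise layer look wrong.

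1. **A test at t0.** At that point the arms have been allocated but not treated. If allocation is random, the null hypothesis is true by design, and a p-value there says nothing about VRET, ACT or usual care. If the FDR adjustment runs over the four listed visits, this null test also tightens the thresholds for the visits that matter.
2. **No use of t0 at t1, t2 and t3.** Craving scores in the same patient are likely to be correlated over time. A one-way ANOVA leaves the part of the follow-up variance that t0 would explain in the error term.

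At stake is the power and readability of the arm comparisons at 4, 12 and 24 weeks. These are the only comparisons in Section 2.10 that say at which visit the arms differ.

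**Working it through.** **The plan's own figure.** The article gives no power for the visit-wise tests. Section 2.2 sizes the trial on the within-between interaction with f = 0.13, 3 groups, 5 measures, alpha 0.05 and power 0.80. With the noncentrality λ = f²·N·m/(1−ρ) and an assumed ρ = 0.5, N = 93 gives λ = 0.0169 × 93 × 5 / 0.5 = 15.7 on 8 and 360 df, and power 0.811. Then 93 × 1.3 = 121, close to the stated 120. So the sample size was set for the main layer and not for the visit-wise tests examined here.

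**Inputs.** From the article: 3 arms, 40 per arm, 4 visits, alpha 0.05. After the planned 30% dropout, 120 × 0.7 = 84, or 28 per arm. Assumed, because the article does not give them: arm means of -0.6, -0.3 and 0 SD (VRET, ACT, control), an equal correlation r between all visits, and the Benjamini-Hochberg procedure for the FDR. These means correspond to f = √[(0.3² + 0² + 0.3²)/3] = 0.245.

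**Gain from adjusting for t0.** ANCOVA multiplies the residual variance by 1 − r², so f becomes f/√(1 − r²).

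| r | 1 − r² | Equivalent gain in patients, 1/(1 − r²) |
|---|---|---|
| 0.3 | 0.91 | 1.10 times |
| 0.5 | 0.75 | 1.33 times |
| 0.7 | 0.51 | 1.96 times |

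Power for one visit from the noncentral F at alpha 0.05 before any FDR step, N = 120:

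| f | One-way ANOVA | ANCOVA, r = 0.3 | r = 0.5 | r = 0.7 |
|---|---|---|---|---|
| 0.13 | 0.22 | 0.24 | 0.29 | 0.40 |
| 0.25 | 0.68 | 0.72 | 0.81 | 0.93 |

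**Cost of t0 in the FDR family.** Benjamini-Hochberg compares the k-th smallest p-value with 0.05·k/m. The first threshold is 0.05/4 = 0.0125 with four visits and 0.05/3 = 0.0167 with three.

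**Both together**, by simulation (20,000 trials per setting), power at t1 with r = 0.5:

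| Setting | ANOVA, FDR over t0–t3 | ANOVA, FDR over t1–t3 | ANCOVA, FDR over t1–t3 |
|---|---|---|---|
| 40 per arm, effect at t1 only | 45% | 49% | 64% |
| 40 per arm, effect at t1, t2 and t3 | 55% | 60% | 75% |
| 28 per arm, effect at t1 only | 29% | 32% | 44% |

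In the first setting, ANCOVA gives 54% at r = 0.3 and 84% at r = 0.7. The unadjusted ANOVA does not depend on r and stays at about 49%. The t0 test costs 49 − 45 = 4, 60 − 55 = 5 and 32 − 29 = 3 points in the three rows.

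**Validity.** With no treatment effect, the chance of any rejection stays at about 5%. The t0 test on its own rejects in about 5% of trials, as a true null should.

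**The main layer in the same setting.** With the effect at t1 only and 40 per arm, the planned interaction test has power of about 50%, 67% and 90% at r = 0.3, 0.5 and 0.7.

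**The case against.** The strongest reply is that Section 2.10 names the mixed ANOVA interaction as the main analysis. There t0 is a level of the within-subject factor, so a chance difference at t0 does not count as a treatment effect. At r = 0.5 with the effect at t1 only, its power (about 67%) is no worse than that of the proposed visit-wise ANCOVA (64%). With the effect at all follow-up visits the order reverses (about 67% against 75%). This stands: the loss falls on supporting comparisons. It does not remove the point, because the interaction is an omnibus test and does not locate the visit.

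Four stronger readings are tempting, and the article does not support them.

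- **That the trial ignores baseline, or would carry a chance t0 difference into its main result.** The mixed ANOVA rules this out.
- **That the t0 test certainly costs power at t1 to t3.** The article does not define the FDR family. Four visits per outcome is a natural reading. If the adjustment runs within a visit, over outcomes or pairs of arms, the t0 test costs the later visits nothing. The loss from ignoring t0 remains either way.
- **That the tests are invalid.** Under randomisation an unadjusted ANOVA keeps its error rate, and adding a true null does not inflate the FDR.
- **That t0 is unusable as a baseline.** Section 2.9 does say "Baseline assessment (t_0_) commences after the randomization of participants into the three intervention groups", and participants are not blinded. When to assess t0 relative to disclosure of the allocation is a separate procedural question. The present point assumes only that t0 precedes treatment and that knowing the allocation does not shift the score.

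It is also fair to say that the gain depends on a correlation that the article does not report. At f = 0.13 and r = 0.5 it is only 0.22 to 0.29 for one visit, though Section 2.2 uses 0.13 for the interaction and not for a single-visit comparison.

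**Conclusion.** The point holds for the visit-wise comparisons only, and as a matter of efficiency and interpretation. The article prescribes a between-arm test at t0 that serves no objective, and follow-up tests that leave out a baseline score already collected.

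Under the assumed effects at t1 only, with 40 per arm and FDR over t1 to t3, ignoring t0 costs about 5 points of power at r = 0.3 (49% against 54%), 15 at r = 0.5 (49% against 64%) and 35 at r = 0.7 (49% against 84%). Keeping t0 in the FDR family costs 3 to 5 points more, if that family is the four visits. The direction does not depend on the exact effect size, but the amount depends on both the effect and r.

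These figures are for a roughly normal score such as PACS. For the drinking measures that refer to the previous week, two weeks of abstinence on the ward (Section 2.6) should leave little spread at t0. The t0 test is then empty and the adjustment gains little. The main mixed ANOVA is unaffected.

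**What to change.** In Section 2.10, or in the statistical analysis plan that Section 2.8 announces:

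1. Report t0 by arm descriptively, without a p-value.
2. Compare the arms at t1, t2 and t3 by ANCOVA with the patient's t0 value of the same outcome as covariate, or by baseline-adjusted contrasts from a longitudinal model. Apply the same to the secondary outcomes.
3. Define the FDR family explicitly and leave t0 out of it.
4. Keep the mixed ANOVA interaction as the main analysis and state that the visit-wise comparisons support it by locating the difference.

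The cost is a change of wording and slightly more analysis work. No new data or visits are needed.

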### 2.2. Sample size

The estimated sample size will be calculated using the G^*^Power 3.1.9.7 sample size calculator, using the sample size calculation for repeated measure ANOVA and within–between interaction, whereby the type I error was 0.05, the power was 0.8, the number of groups was three (VRET, ACT, and TAU groups), the number of measures was five (degree of alcohol craving, severity of alcohol use disorder, depression symptoms, anxiety symptoms, and changes in ERP), and the effect size was 0.13, which was cited from a randomized clinical trial that compared the efficacy of virtual reality therapy with multisensory stimulation and cognitive behavioral therapy in alleviating alcohol craving in alcohol dependence patients (32). The estimated total sample size needed was 120 (after inclusion of 30% dropout), in which 40 subjects per group are required.

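### At the planned 30% dropout, an untestable judgement about why data are missing picks the primary analysis, and the non-random branch uses only the remaining data with no sensitivity analysis

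*Protocol article*

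**What the plan says.** Section 2.10 (Data analysis) makes a mixed ANOVA of intervention by time over four assessments the main analysis, and states: "The primary outcome assessment will follow the intent-to-treat principle". It then sets the missing-data rule:

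- Up to 5% missing: ignored.
- From 5 to 40% missing and judged missing at random: "multiple imputations with restricted maximum likelihood estimates will be performed using Stata 15".
- Otherwise: "if the missing data are more than 40% or are completely randomly missing or non-randomly missing, data analysis of the remaining data will proceed". The only further step is to report the matter as a limitation.

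Section 2.2 (Sample size) gives the expected loss: "The estimated total sample size needed was 120 (after inclusion of 30% dropout".

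Section 4 (Ethics and dissemination) adds that data already collected from a participant who withdraws are discarded, and that participants with adverse effects are withdrawn from the study.

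**The concern.** The rule chooses the method by the missingness mechanism. Missing at random and missing not at random differ in whether dropout depends on values nobody has seen, so no test on the observed data can tell them apart. The analyst would settle the matter after seeing the data, and the primary result could depend on it.

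The branch for non-random missingness is the one where an observed-data comparison is most open to bias. Here it receives neither imputation nor a sensitivity analysis, and a limitation paragraph does not correct an estimate. Sections 1.1 and 1.5 describe craving as the driver of relapse, so dropout related to craving, the primary outcome, is plausible over 24 weeks. Randomised participants would then fall out of a comparison declared intent-to-treat.

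**Working it through.** **The plan's own figure.** Inputs from section 2.2: "the type I error was 0.05, the power was 0.8, the number of groups was three"; "the number of measures was five"; "the effect size was 0.13". The correlation between measures is not stated; 0.5 is assumed. With λ = f²·N·m/(1−ρ), df1 = (k−1)(m−1) and df2 = (N−k)(m−1), 80% power needs N = 91, or 93 in multiples of three. Then 91 × 1.3 = 118.3 and 93 × 1.3 = 120.9, which agrees with 120. The figure is not at issue here; it fixes the expected loss at 0.30 × 120 = 36 participants.

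**Which branch applies at that loss.** The base of the percentage is not defined, so take each reading:

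- Participants: 36/120 = 30%.
- PACS values out of 120 × 4 = 480, each dropout missing one to three assessments: 36/480 = 7.5% to 108/480 = 22.5%.
- The same, if all four values of each dropout are discarded: 144/480 = 30%.

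All lie between 5 and 40%. The percentage therefore does not decide; the judged mechanism does. Missing at random leads to imputation, and completely random or non-random leads to the remaining data.

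**Size of the possible bias.** The documents give no PACS SD, mechanism or dropout by arm, so these are assumptions. Final PACS is normal with SD 1, mean 0 in TAU and −0.5 in VRET, and average dropout is 30%.

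*Logistic dropout.* P(drop | y) = 1/(1 + exp(−(a + βy))), with a set to give 30% on average. The completer mean is ∫y(1−P)φ(y−μ)dy / ∫(1−P)φ(y−μ)dy.

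*Threshold dropout (extreme).* Everyone above c leaves, and the completer mean is μ − φ(c−μ)/Φ(c−μ). With c = 0.291, TAU gives −0.622 (38.6% dropout) and VRET gives −0.5 − 0.371 = −0.871 (21.4% dropout). The difference is −0.249.

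*Missing-at-random comparison.* Regress final PACS on baseline among completers within each arm, then average the predictions over everyone randomised. The baseline-to-final correlation is assumed to be 0.5 or 0.7.

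| Dropout related to craving | Complete cases | Missing-at-random, corr. 0.5 | Missing-at-random, corr. 0.7 |
|---|---|---|---|
| β = 0.5 (odds × 1.6 per SD) | −0.48 | −0.48 | −0.49 |
| β = 1.0 (odds × 2.7) | −0.43 | −0.44 | −0.46 |
| β = 1.5 (odds × 4.5) | −0.39 | −0.41 | −0.43 |
| Threshold | −0.25 | −0.27 | −0.30 |

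**With no true effect** (simulated, correlation 0.5):

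- Dropout of 40% against 20%, same slope in both arms: complete cases show a spurious difference of about 0.09 SD (β = 0.5) or 0.16 SD (β = 1.0), in favour of the arm that loses more. Missing-at-random leaves 0.07 and 0.13.
- Dropout of 30% in both arms, related to craving (β = 1.0) in one arm only: 0.25 SD; missing-at-random leaves 0.20.
- Same rate and same mechanism in both arms: about 0.
- Completely random dropout, even at unequal rates: 0.

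**Precision in the remaining-data branch.** If 36 are lost, N = 84. With m = 5, λ = 0.0169 × 84 × 5/0.5 = 14.2 and power is 0.76. With m = 4, the number of assessments, λ = 11.4 and power is 0.70. This cost arises even when nothing is biased.

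**The case against.** The rule is better than a quick reading suggests, and several stronger inferences fail.

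- *The fallback is reserved for non-random data.* It is not. It also covers completely random missingness, where remaining data are unbiased and only power is lost, and anything above 40%.
- *The trial will lose 36 of 120 from its analysis.* Only if the missingness is judged completely random or non-random. If judged random, the middle tier imputes and the mixed ANOVA receives completed data. Even in the fallback, dropping everyone with a missed visit assumes the classical complete-data mixed ANOVA. The article names SPSS and mixed ANOVA, not the procedure.
- *The fallback itself costs 5 to 50% of the effect.* The table does not show that. A missing-at-random analysis has most of the same shortfall, though intermediate visits, not modelled here, might recover more. The figures mainly support adding a non-random sensitivity analysis.
- *Imputation combined with restricted maximum likelihood cannot be run.* Too strong. Imputing from a model fitted that way is conceivable; the wording is unclear.
- *Intent-to-treat is flatly contradicted.* If it means only analysis by allocated arm, an observed-data analysis is compatible with it. The clearer conflict is with section 4, where withdrawn participants' data are discarded.

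Craving-driven dropout is also an assumption. The reasons listed in section 2.9.3.5 are lack of interest, illness, transport and logistics. What stands is that the mechanism judgement is untestable and that the non-random branch has no sensitivity analysis.

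**Conclusion.** The concern holds in this limited form. At the protocol's own expected dropout, the primary missing-data method turns on a distinction the data cannot make, and one of the two outcomes of that judgement is an unsupported remaining-data analysis. That can bias the group comparison when dropout differs by arm, in either direction. In the illustrations a true −0.5 SD shrinks by 0.02 to 0.11 SD under graded dropout and by 0.25 SD in the extreme case, and a null effect can appear as 0.09 to 0.25 SD. These sizes rest on the assumed SD, slopes, dropout rates and correlations, and they vanish if rate and mechanism are the same in all arms. A reader might infer that the present plan is certain to give a biased or completers-only result; the documents do not support that. This is a rule the article itself states, not a detail left to an analysis plan, so it should be settled before analysis.

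**What to change.** Replace the rule in section 2.10 with one primary analysis: a likelihood-based (REML) mixed model for repeated measures on all observed PACS values of all randomised participants, whatever the percentage missing. Because that model also assumes missing at random, add one pre-specified missing-not-at-random sensitivity analysis: delta-adjusted or control-based multiple imputation, carried to a tipping point. Delete the remaining-data fallback. Where multiple imputation is kept, state the imputation model and the analysis model separately, so that the role of restricted maximum likelihood is clear. Reconcile the intent-to-treat statement with section 4 on discarding withdrawn participants' data and on withdrawal after adverse effects.

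The cost is a change of wording, its report to the two ethics committees as section 4 requires for changes in data analysis, and a little more analysis work. SPSS 26 and Stata 15, both already named, can fit the model.

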### 2.11. Data availability

Anonymous data will be made available after the publication of the findings of the study. The data will be uploaded to the Figshare data repository after the completion of the study.

## 3. Discussion

This study primarily investigates the efficacy of VRET compared with ACT and treatment as usual to depreciate the degree of alcohol craving for people with alcohol use disorder to reduce relapse. In addition, this study also evaluates the efficacy of VRET compared with ACT and treatment as usual to dissipate the severity of alcohol use disorder, and comorbid depressive and anxiety symptoms and normalize the ERP among the alcohol use disorder patients across four timelines (from the baseline to immediately after completion of intervention, 8 weeks after completion, and 20 weeks after completion). The research findings will provide evidence to treating clinicians regarding efficacious psychotherapy or psychosocial intervention for the treatment of alcohol use disorder to reduce the rate of relapse, in which currently available pharmacotherapy has little success. Moreover, if VRET and ACT are proven efficacious to treat alcohol craving, these interventions should also be investigated for their efficacy to treat craving and prevent relapse in other substance use disorders in the near future, whereby the methodology of this RCT could be replicated in future studies.

There are a few limitations to be considered in this study. First, this study only recruits male alcohol use disorder patients, which may limit the generalizability of the study findings as it may not be representative of the entire alcohol use disorder population in China and Malaysia. Second, this study will only recruit subjects with Han ethnicity in China and Malaysian Chinese, which may not be representative of the alcohol use disorder population in China and Malaysia as both countries' populations consist of multi-ethnic background. Finally, the differences in the scheduling of interventions and duration of the session between the VRET and ACT groups may lead to differences in findings due to discrepancies in the settings rather than due to differences in efficacy between the two interventions. However, we attempted to align the scheduling of the sessions in all the three groups as similarly as possible. VRET is scheduled for 25 min/session, five times a week for 20 sessions (total duration = 4 weeks), ACT will be conducted for 1 h/session, two times a week for eight sessions (total duration = 4 weeks), and the control group session is performed at 1 h/session, two times a week for eight sessions (total duration = 4 weeks).

